## Objectives of the study and expected outcomes

The specific objectives of this project are the following:To test the short- and long-term efficacy of the program in preventing weight regain and promoting weight loss maintenance, promoting new eating behaviors, decreasing psychological distress, enhancing individual self-concept, and addressing other psychological outcomes.To test the utility, feasibility, and perceived satisfaction with APOLO-Bari in terms of compliance with proposed tasks, log-in frequency, and direct evaluation of the satisfaction of participants. Participants with higher log-in frequency and compliance with monthly assessments are expected to report better weight outcomes, higher levels of satisfaction with weight loss and surgical treatment, and lower scores on the self-reported measures, thus reflecting better psychosocial functioning.To study weight regain by exploring the temporal courses of eating-related features and predictors of weight regain. We expect to identify fluctuations in key behaviors that precede weight regain.

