### Informed consent and randomization

Those who agree to participate in the study will have a computer connected to the internet, and each participant will complete the informed consent form online and register in the program by creating a personal username and password. All participants will complete an initial short sociodemographic and clinical questionnaire (see details in the measures section). To ensure concealment of allocation, the APOLO-Bari system will then automatically randomize (computer-generating random numbers) the participants on a 1:1 basis, matching for age, sex, and surgery type.

After randomization, intervention group members will receive full access to the three components of the APOLO-Bari program in their personal accounts. The intervention will last for 12 months, and a 6-month period will follow, with no program access possible. During the intervention period, the system will record data on log-in frequency, task submission, and weekly monitoring from the intervention group.

The control group will only have access to general information on obesity and bariatric surgery and to the set of self-report measures at the different assessment times. The control group participants will be informed of the assessment times and the possibility of accessing the full program after the study is complete. Both groups will receive reminder emails every time a questionnaire or activity is available.

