### Psychological self-report measures

Repetitive Eating Questionnaire [12]: This self-report questionnaire assesses a grazing-type eating pattern through 15 items, resulting in two subscales that reflect compulsive grazing and non-compulsive grazing subtypes.

Depression Anxiety Stress Scales [36]: This 21-item questionnaire generates subscales on depression, anxiety, and stress.

Eating Disorder – 15 [37]: This 15-item questionnaire assesses eating disorder cognition and behaviors, with subscales for weight and shape concerns and for eating concerns.

Negative Urgency Subscale [38]: This 12-item scale assesses an individual’s tendency to surrender to strong impulses, particularly when accompanied by negative emotions, such as depression, anxiety, or anger.

Influence of weight: Developed by the research team, this 12-item measure inquires about the influence of weight in different areas of life (e.g., intimate relationships, professional roles, self-esteem).

Satisfaction questionnaire: Developed by the research team, this 19-item questionnaire addresses the utility and feasibility of the program from the patient’s perspective.

All questionnaires have been used with this sample by the research team in previous studies, and show good internal consistency for use with bariatric surgery patients.

Table 3 presents a summary of the self-report measures used for each group at each assessment time.

**Table 3 Tab3:** Timeline for the self-report measures

	Registration	Baseline (*T* _b_)	4-month midterm assessment (*T* _m4_)	8-month midterm assessment (*T* _m8_)	Final (end of treatment) assessment (*T* _f_)	6-month follow-up assessment (*T* _fu6_)	12-month follow-up assessment (*T* _fu12_)	Weekly
Sociodemographic weight history	X	–	–	–	–	–	–	–
Clinical inventory	–	X	X	X	X	X	X	–
Repetitive Eating Questionnaire [12]	–	X	X	X	X	X	X	–
Depression Anxiety Stress Scales [36]	–	X	X	X	X	X	X	–
Eating Disorder – 15 [37]	–	X	X	X	X	X	X	–
Negative Urgency Subscale [38]	–	X	X	X	X	X	X	–
Influence of weight	–	X	X	X	X	X	X	–
Satisfaction questionnaire	–	–	–	–	Intervention group	–	–	–
Eating and exercise behaviors (Table 4)	–	Control group	Control group	Control group	Control group	X	X	Intervention group

*X* available for both intervention and control group

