### Statistics

Pearson’s chi-square tests will be used to analyze significant differences in the proportion of cases with weight regain and in specific outcome variables between the intervention group and the control group. Significant weight regain will be considered when higher than 5 kg. The Kaplan–Meier approach (together with the log-rank test) will be used to answer the main question of efficacy. Repeated-measures analysis of variance (ANOVA) will be conducted to explore differences between the participant groups for different key variables at various time points. The main effect for surgery type will be investigated. Variables such as log-in frequency, task submission, satisfaction with the program, socio-demographics, pre-intervention scores on self-report measures, and time since surgery will be tested as covariates and predictors of outcomes using Cox regression models. Relevant baseline differences will be included as covariates. Hierarchical linear models will be used to investigate different trajectories of relevant variables assessed from *T*_b_ to *T*_fu12._ Hierarchical linear models are the models that best fit unbalanced designs with unequal number of observations (missing data) per subject. Self-report measures (for depression, impulsiveness, eating disorder and eating patterns, body image, and general distress) will be examined by conducting an analysis of covariance to explore interference with weight outcomes. Post-hoc comparisons will be conducted using Tukey’s procedure. Controlled effect sizes will be calculated using the Cohen’s *d* statistic.

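### Log-in frequency, task submission and end-of-treatment satisfaction enter Cox models beside baseline variables, though they arise after randomization, in one arm only, and partly or wholly after regain can already be detected

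*Protocol article*

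**What the plan says.** The Statistics section of the protocol article lists "Variables such as log-in frequency, task submission, satisfaction with the program" together with socio-demographics, pre-intervention questionnaire scores and time since surgery. It says that all of these "will be tested as covariates and predictors of outcomes using Cox regression models". It does not separate variables known at randomization from those that arise later.

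Other sections show what the first three variables are:
- Informed consent and randomization: during the intervention period "the system will record data on log-in frequency, task submission, and weekly monitoring from the intervention group". On duration: "The intervention will last for 12 months".
- The same section, on controls: "The control group will only have access to general information on obesity and bariatric surgery and to the set of self-report measures".
- Table 3 (Psychological self-report measures) schedules satisfaction once, at the end-of-treatment visit T_f, in one arm: "Satisfaction questionnaire – – – – Intervention group".
- Anthropometric measures: the research team measures weight in both arms at baseline, months 4, 8 and 12, and both follow-ups.
- Objectives, second objective: "Participants with higher log-in frequency and compliance with monthly assessments are expected to report better weight outcomes".

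The main efficacy question is assigned to Kaplan–Meier curves with a log-rank test.

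**The concern.** A Cox model with a fixed covariate compares, at each event time, the covariate of the person who has the event with the covariates of those still at risk. The covariate must therefore be known before the event. A 12-month log-in total, or a score taken at month 12, is not known at month 4 or 8. If regain changes how often people log in or how satisfied they are, the outcome leaks into its own predictor.

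The second objective states in advance that heavier users are expected to do better. An association produced by reverse causation could then be taken as confirmation. Separately, a model containing both arms has no value of these variables for controls.

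**Working it through.** No figure stated in the plan is at issue. The check is one of timing, followed by simulations that show what the timing can do.

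**1. Timing and arm**

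| Variable | Arm | Complete at | Visits where regain can be detected before or at that time |
|---|---|---|---|
| Log-in frequency, task submission | intervention | month 12 | months 4, 8, 12 |
| Satisfaction | intervention | month 12, single measurement | months 4, 8, 12 |

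**2. Share of events too early to be predicted**

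Assumptions: the event is regain above 5 kg (Statistics section); constant hazard; 24-month risk p of 30, 37 or 50 %. The Background's 37 % uses another definition of regain and no 24-month horizon, so it serves only as an illustration.

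Share detected by month m = [1 − (1 − p)^(m/24)] / p.
- p = 0.37, m = 8: (1 − 0.63^(1/3)) / 0.37 = 0.39.
- p = 0.37, m = 12: (1 − 0.63^(1/2)) / 0.37 = 0.56.
- For p = 0.30 and 0.50 the shares are 37 % and 41 % by month 8, and 54 % and 59 % by month 12.

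**3. Within the intervention arm, true effect of use zero**

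90 per arm less 20 % dropout = 72 completers; visits at months 4, 8, 12, 18 and 24; weekly log-ins averaging 1 and varying between people (gamma shape 4), independent of the hazard; Cox model on the 12-month total; 600 runs per setting.

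| Log-ins after regain | Median HR per 10 log-ins | p < 0.05, 37 % risk | p < 0.05, 30 % risk |
|---|---|---|---|
| unchanged | 1.00 | 4.5 % | 6.7 % |
| fall by a quarter | 0.94 | 7.8 % | 7.3 % |
| halve | 0.89 | 25.7 % | 22.5 % |

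Satisfaction lowered by 0.5 SD in those who regained by month 12 gave an HR of 0.77 to 0.80 per SD, significant in 20 to 27 % of runs.

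A second set-up used 90 participants, 37 % risk by 12 months, a mean of 52 log-ins and 300 runs. Halving gave 22, 43, 81 and 97 % false positives for gamma shapes 1, 2, 4 and 10. No change gave 5 to 8 %. A 25 % rise after regain gave HRs of 1.14 to 1.37, so the sign reversed. One reason for the higher rates is that all of about 90 × 0.37 = 33 events fall inside the 12 months, against about 72 × 0.37 × 0.56 = 15 in the first set-up.

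**4. If both arms were in one model, controls coded zero**

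37 % risk, 72 per arm, 600 runs. Cells show median treatment HR / rejection rate / SE.

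| True HR; log-ins after regain | Arm only | Arm plus log-ins |
|---|---|---|
| 1.0; unchanged | 0.99 / 5 % / 0.28 | 1.00 / 6 % / 0.47 |
| 1.0; halve | 1.01 / 4 % / 0.28 | 1.84 / 26 % / 0.47 |
| 0.5; unchanged | 0.51 / 56 % / 0.33 | 0.50 / 18 % / 0.62 |
| 0.5; halve | 0.49 / 61 % / 0.33 | 0.86 / 5 % / 0.61 |

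The arm-only results for a true HR of 0.5 differ (56 and 61 %) only by simulation error. The loss of precision needs no change in behaviour after regain. If control values were left missing instead, every control would drop out of the model.

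**The case against.** The strongest reply is that these models are an exploratory look at program users. Controls have no recorded log-ins, no tasks and no satisfaction form, and the second objective concerns utility and feasibility. That is a natural reading, and it removes the two-arm problem. It does not remove the timing problem, which exists inside the intervention arm.

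It can also be said that landmarks, lags and arm restrictions belong in an analysis plan that is not shown. The article respects time order elsewhere: midterm secondary outcomes are to predict later weight outcomes, and moderators and nonspecific predictors are taken at baseline. But neither rule covers these three variables, and the Statistics section positively places them with baseline covariates. The point concerns what is stated, not missing detail.

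Four stronger readings are tempting and not supported:
- A reader might infer that the trial's treatment effect is biased. The main efficacy question rests on Kaplan–Meier and log-rank, and no treatment effect is said to be read from these Cox models.
- A reader might infer that regain ends program use. It does not: the alarm in the feedback section leads to an email contact, and under Safety aspects a participant in individual support may continue unless the specialist asks otherwise.
- A reader might infer that the bias must favour the program. Contact after an alarm could raise use, which reverses the sign.
- A reader might take one simulated error rate as this trial's rate. The range above shows how far it depends on assumptions.

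**Conclusion.** The point holds for the Cox analyses of use and satisfaction. That the variables are post-randomization, recorded in one arm and partly or wholly later than detectable events follows from the document without any assumption. For satisfaction the fault is plainest: a score taken at month 12 cannot predict regain seen at month 4 or 8.

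The consequence is that the use–outcome association in the second objective could not be interpreted if these were fitted as ordinary fixed covariates. Its size and direction depend on how use and satisfaction change after regain, on event risk and on variation in log-ins, none of which the document gives. False-positive rates run from about nominal to well above 5 %. The distortion of a treatment coefficient is conditional on someone fitting the two-arm model, which the protocol neither specifies nor excludes.

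**What to change.** - In any Cox model that compares the arms, allow only covariates fixed before randomization.
- Analyse log-ins and task submission within the intervention arm only. Either use a landmark (for example, use in months 0–4 predicting regain after the month-4 visit among those event-free then) or time-varying values lagged to the preceding assessment. A total counted up to the event is no substitute, because those who stay event-free longer have more time to log in.
- Use month-12 satisfaction only for outcomes after month 12, or simply describe it.
- Label all these results exploratory and associational.

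The cost is wording, a little extra analysis on data already being collected, and fewer events. With 72 completers, constant hazard and 37 % risk (72 × 0.37 = 27 events), a month-4 landmark drops (1 − 0.63^(1/6)) / 0.37 = 20 % and leaves about 21 events. A month-12 landmark drops 56 % and leaves about 12. At 30 % risk, about 17 and 10 of 22 remain. The satisfaction analysis in particular will be imprecise. The trial was still recruiting when the article was written, so the change could be made before any analysis.

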#### Self-report questionnaires

##### Sociodemographic and weight history

This history assesses data on the demographic information (sex, age, and marital status) and relevant clinical variables (type of surgery, pre-surgery weight, lowest and highest weight before surgery, lowest weight achieved after surgery).

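### Covariates are to be picked from observed baseline differences, and the main efficacy tests are not stated to use the randomization factors or baseline weight

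*Protocol article*

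**What the plan says.** All references are to the protocol article.

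- **Allocation.** Under Informed consent and randomization, the system allocates 1:1, "matching for age, sex, and surgery type". How the matching is carried out is not described.
- **Main tests.** Under Statistics, "The Kaplan–Meier approach (together with the log-rank test) will be used to answer the main question of efficacy". Also, "Pearson’s chi-square tests will be used to analyze significant differences in the proportion of cases with weight regain". Neither test is described as stratified or adjusted.
- **Covariate rule.** The same section adds: "Relevant baseline differences will be included as covariates". It does not say what makes a difference relevant, which variables are candidates, or which analyses receive the covariates.
- **Other uses of the same variables.** Under Statistics, "The main effect for surgery type will be investigated", and "socio-demographics, pre-intervention scores on self-report measures, and time since surgery will be tested as covariates and predictors of outcomes using Cox regression models". Sociodemographic and weight history places sex and age among the demographic items. Primary and secondary outcome measures lists surgery type and sex among the baseline moderators and predictors.
- **Baseline weight.** It is measured by the research team at T_b (Anthropometric measures). T_b is one of the time points in the group comparisons and in the hierarchical models that run to the 12-month follow-up. T_b weight is never named as a covariate.

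**The concern.** A baseline difference in a properly randomized trial arises by chance. A rule that adjusts for whatever happens to differ makes the model depend on the data and chooses variables by imbalance, when what matters is how strongly a variable predicts the outcome. It also works against the design: factors balanced by the allocation will seldom differ, so the rule will seldom pick them.

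Three things are at stake. First, precision: prognostic information that is already collected is not used in the tests that carry the efficacy conclusion. Second, calibration: a test that leaves out prognostic factors balanced by design, or adjusts only on imbalance, does not run at its nominal level. Third, openness to choice: because *relevant* is undefined, several adjusted results could each be defended after the data are seen.

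**Working it through.** The covariate rule contains no figure to reproduce. The check asks how often chance would trigger the rule, what it does to type I error, and how much precision is left unused.

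**Inputs from the article** (Proposed sample size and power calculations): 90 per group, 20% dropout, alpha 0.05. Evaluable per arm: 90 × 0.8 = 72, or 144 in total.

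**Assumptions, not in the article:**
- Standardized difference d = 0.4. The article gives an effect size of 0.2 without a metric; d = 0.4 is what Cohen's f = 0.2 means for two groups (d = 2f).
- Two-sided testing.
- Correlation r between the T_b value and the outcome of 0.3 to 0.7.
- A prognostic effect of 0 or 0.5 SD for each of two balanced factors.

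**1. How often chance triggers the rule.** If a difference counts at p < 0.05 and there are k independent baseline variables, the chance of at least one is 1 − 0.95^k: 0.23 for k = 5, 0.40 for k = 10 and 0.54 for k = 15.

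**2. Unused precision, continuous outcome.** Adjusting for a covariate with correlation r multiplies the residual variance by 1 − r². By the normal approximation, power = Φ(d·√(n/2)/√(1 − r²) − 1.96), with d·√(n/2) = 0.4 × √36 = 2.4.

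| r | 1 − r² | 2.4/√(1 − r²) | Power |
|---|---|---|---|
| unadjusted | 1 | 2.40 | 0.67 |
| 0.3 | 0.91 | 2.52 | 0.71 |
| 0.5 | 0.75 | 2.77 | 0.79 |
| 0.7 | 0.51 | 3.36 | 0.92 |

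The non-central t gives 0.66 for the unadjusted case and the same rounded values at r = 0.5 and 0.7.

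**3. Type I error and power by simulation.** Settings: N = 144, continuous outcome, 1:1 allocation balanced within the four cells of two binary factors, five baseline covariates, 6,000 null runs and 3,000 runs at d = 0.4 per setting. The Monte Carlo standard error at 0.05 is √(0.05 × 0.95/6000) = 0.003. *Fixed* means both factors plus the baseline value, named in advance. *Best of several* means the most favourable covariate set, chosen after seeing results.

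| r; effect of each factor | Unadjusted | Fixed | Select p < 0.05 | Select p < 0.20 | Best of several |
|---|---|---|---|---|---|
| Type I error: 0.5; 0.5 SD | 0.035 | 0.044 | 0.025 | 0.015 | 0.072 |
| Type I error: 0.7; 0 SD | 0.049 | 0.048 | 0.027 | 0.015 | 0.109 |
| Type I error: 0.7; 0.5 SD | 0.034 | 0.052 | 0.018 | 0.006 | 0.078 |
| Power: 0.5; 0.5 SD | 0.66 | 0.85 | 0.67 | 0.72 | – |
| Power: 0.7; 0 SD | 0.66 | 0.90 | 0.69 | 0.75 | – |
| Power: 0.7; 0.5 SD | 0.68 | 0.97 | 0.70 | 0.77 | – |

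Over all settings examined, type I error was:
- fixed adjustment: 0.044–0.052;
- p < 0.05 rule: 0.018–0.046;
- p < 0.20 rule: 0.006–0.037;
- unadjusted: 0.030–0.035 with prognostic factors, about 0.05 without;
- best of several: 0.06–0.11.

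The downward direction has a simple cause. Selection on imbalance removes false positives that the imbalance would have produced, while the remaining runs keep a standard error that is too large. Power under the p < 0.05 rule was 0.67–0.70, so that rule recovers almost none of the available gain; the looser threshold recovers part of it.

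**The case against.** The strongest reply is that the harm is smaller than it looks, and much of that reply stands.

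- **The error rates are not invalid.** A reader might infer that choosing covariates from the data inflates type I error. Under any mechanical rule examined here the error was at or below 0.05. Inflation needs a choice informed by the results, which the article leaves possible but does not propose.
- **The factors are not ignored.** A reader might infer that age, sex, surgery type and the T_b value play no part in the analysis. They do: there is a surgery-type main effect, socio-demographics enter Cox models, sex and surgery type are listed as moderators, and T_b is a time point in the longitudinal analyses. None of this fixes adjustment in the log-rank or chi-square test. The Cox models also mix baseline variables with post-randomization ones such as log-in frequency and satisfaction.
- **The power figures do not describe the main tests.** The 1 − r² reduction belongs to a continuous outcome and does not carry over to log-rank, Cox, chi-square or logistic analyses. The correlations are assumed. Because the Subjects section excludes patients with more than 15% regain at registration, the T_b regain value has a restricted range, so the lower correlations deserve weight.
- **The sentence may be narrower than it reads.** It follows the Cox sentence and may apply only there; *relevant* may mean prognostic; dropout may disturb the balance, so matched factors could occasionally be selected. These are reasons to define the rule.
- **A separate analysis plan may list covariates.** It may, but the article states the selection rule positively, and a plan that followed it would carry the same weakness.

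**Conclusion.** The point holds in limited form. The stated rule is data-driven and undefined, it will rarely select the factors balanced at randomization, and the tests named for the main efficacy question and the proportion with regain are not stated to use those factors or T_b weight. The consequences are lost precision, a type I error off its nominal value (mostly conservative) and room for selective adjustment. The documents do not support a claim that error rates are generally invalid or that the variables go unused.

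The illustrated gain, from about 0.67 to between 0.71 and 0.92, rests on a continuous outcome, an assumed d of 0.4, 72 per arm and an assumed r of 0.3 to 0.7. For the log-rank and chi-square tests the size will differ and cannot be derived from the article.

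**What to change.** Delete the baseline-difference sentence. Name age, sex, surgery type and one T_b weight measure in advance as covariates or strata in the main between-group analyses:

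- **Main efficacy question:** a log-rank test stratified by sex and surgery type, or a Cox model with the named covariates. Choose one now.
- **Proportion with regain:** logistic regression with the same covariates in place of Pearson's chi-square.
- **Continuous outcomes:** adjust for the T_b value in models of post-baseline outcomes. Where T_b is already a response time point, do not also enter it as a covariate.
- **Sensitivity:** report the unadjusted results.

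The variables are already collected, so no extra patients or visits are needed. The cost is slightly more analysis work, and adjusted Cox and logistic estimates are conditional effects, which the report should say. Because this changes the named main tests, it should be recorded as a trial modification before outcome data are examined; Trial status says recruitment is not complete.
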